### California Healthy Kids Survey Data–Community-Level Youth Sample

#### Collecting and Accessing Data From the California Healthy Kids Survey

This study also used the California Healthy Kids Survey (CHKS) as a mechanism for collecting evaluation data. CHKS collects school-climate data from in-school youth attending public high schools across California. Researchers and Local Educational Agencies are able to develop and build custom data collection modules as part of the CHKS system. In summer 2021, the research team developed a custom module focused on SV prevention to be included in CHKS, which was made up of an abbreviated set of measures used in the SN data collection, and WestEd integrated it into their survey system. Before and during the 2021 to 2022 and 2022 to 2023 academic years (timing guided by SN data collection for each C2H or control group) and with guidance from WestEd, the research team conducted school recruitment by contacting school district leaders and school principals from schools in the targeted zip codes of study communities via email and telephone on multiple occasions with a description of the research and incentives for schools (US $300 gift card, fees covered). For schools or districts that responded, we conducted an informational call about the purpose of the module, the risks and benefits to the school, and implementation logistics, including that implementation of the module would be requested again in 2 years. We then coordinated with WestEd to ensure the opted-in schools received the module, and schools scheduled a date for implementation. Voluntary opt-out parental consent that included specific language about the SV module was obtained by providing informed consent to students’ parents via school parent portals or websites before implementation, per WestEd protocols. Schools implemented the CHKS core and optional SV modules during one class period with all 9th- and 11th-grade students, which took about 50 minutes. Informed assent and data were collected via an online survey that was administered by teachers and/or school staff with training and protocols provided by WestEd. Students received no incentives for participation. The survey was anonymous and did not collect identifying information from students. A data use agreement with the research team’s institutions, WestEd and the California Department of Education, guided the secure transfer of data from the relevant school years to the research team, and are stored on a protected and secure server.

#### Follow-Up CHKS Data Collection

All schools that participated in baseline CHKS data collection in 2021‐2022 or 2022‐2023 were recruited for 24-month follow-up CHKS data collection in the academic year that included the 24-month follow-up period for each specific study community. Similar recruitment methods to those used in baseline recruitment were used, as many of the administrators have changed over the two years. Implementation, informed consent, and data transfers under new data use agreements were also conducted in the same way as baseline.

#### CHKS Data Statistical Power

We estimated that we would have a sample of 6 C2H schools and 6 control sites at 24-month follow-up for CHKS administration, with an average of 500 students per school, which would provide data from an estimated 6000 students. We assumed control students would have the same past 12-month incidence of SV at follow-up as what has been observed to date in baseline, which would provide sufficient power to detect a 14.5% reduction in SV (reduced from 13.8%, 414/3000, to 11.4%, 343/3000) in the treatment group. It is reasonable that such a reduction in SV is possible, given previous studies [40,41]. We acknowledged that power calculations may vary depending on actual intercluster correlations and the number of schools.

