##### SN Data Statistical Power

We powered the matched cluster evaluation trial to have .80 power to detect a reduction in 12-month incident SV (the primary outcome) at α<.05. We estimated we would have a follow-up sample of 791 youth study participants (baseline sample: n=953, 791/953, estimated 85% retention at follow-up) from the SN data collection across 22 study sites (11 C2H and 11 control; estimated 36 youth per cluster). We assumed that the average baseline 12-month incidence of the primary outcome would remain constant for the control group at follow-up (107/395, 27% past 12 months SV). The minimal detectable effect would therefore be a 32% (.27 × .32) reduction in SV (71/396, 18% for 12 months incidence at follow-up). Reducing SV by 32% is feasible, given that a previous rigorous evaluation of the shifting boundaries SV prevention model detected a 43% and 50% reduction in SV [40,41]. Furthermore, 37.5% (297/791) of the sample identified as a sexual and/or gender minority (ie, LGBTQ+), among whom 42.4% (126/297) report SV. Estimating the minimal detectable effect for this subsample (297/791 of follow-up participants, 37.5%, 14 LGBTQ+ youth per site), and a 42.5% baseline incidence for LGBTQ+ controls, this study was also powered to detect a 33.5% (0.335 × 0.425=0.14; 0.425-0.14=28% for 12 months incidence at follow-up, 83/297) reduction in LGBTQ+ SV experiences.

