#### Analyses of California Healthy Kids Survey Data

The CHKS is representative of in-school youth attending public schools within the target communities of the C2H and control programs (86 per every 100 youth, 86%, participates at study site schools). We estimate that we will have 6 intervention and 6 control schools who participate in both baseline and 24-month follow-up, each with 500 students on average. Difference-in-differences hierarchical models will be used to estimate the impact of the C2H program on primary and secondary outcomes, relative to control program communities, controlling for confounders and accounting for clustering at the school level. If statistical power allows, we will assess for modification due to gender, LGBTQ+ identity, race or ethnicity, implementation quality, and program site. Sensitivity analyses will be conducted to assess the variability of effects due to any potential violations of the parallel trend assumption and bias due to potential uneven inclusion across intervention and control schools.

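### The school-survey (CHKS) power statement gives a 14.5% detectable reduction where its own rates give about 17%, and those rates appear to make no allowance for clustering in 12 schools

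*Protocol article*

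**What the plan says.** In the protocol article, CHKS Data Statistical Power expects "a sample of 6 C2H schools and 6 control sites at 24-month follow-up for CHKS administration", with about 500 students per school and 6,000 in all. It takes the control rate at follow-up to equal the rate seen so far at baseline, and claims "sufficient power to detect a 14.5% reduction in SV (reduced from 13.8%, 414/3000, to 11.4%, 343/3000) in the treatment group". It gives no power level, alpha, ICC or design effect. It closes with a caveat: "We acknowledged that power calculations may vary depending on actual intercluster correlations and the number of schools".

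SN Data Statistical Power, which concerns the other sample, was set "to have .80 power to detect a reduction in 12-month incident SV (the primary outcome) at α<.05". Analyses of California Healthy Kids Survey Data states the planned method: "Difference-in-differences hierarchical models will be used to estimate the impact of the C2H program on primary and secondary outcomes", with clustering handled at school level. The section on collecting CHKS data says the survey is anonymous and is given to 9th and 11th graders.

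**The concern.** Two things look wrong. First, the headline percentage does not follow from the rates and counts printed beside it, and it errs in the favourable direction by claiming sensitivity to a smaller effect than those rates represent. Second, the rates look like the output of a calculation that treats 6,000 students as independent, whereas the intervention is delivered to communities and only 12 schools are expected. With about 500 students per school, even a very small ICC removes much of the information.

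CHKS is one of the two sources meant to show effects beyond programme participants. A reader who trusts the printed figure could take a null CHKS result as evidence against a reduction of about 15%, which this design may have little chance of detecting.

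**Working it through.** **Inputs.** From CHKS Data Statistical Power: 13.8% (414/3000), 11.4% (343/3000), 14.5%, 6 schools per arm, 500 students per school. From SN Data Statistical Power: power .80 and alpha .05. Assumed: a two-sided test, all ICC values, and all between-wave correlations; the article gives none of these.

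**1. Relative reduction.**
- From the percentages: 1 − 0.114/0.138 = 17.4%.
- From the counts: 1 − 343/414 = 17.1%.
- Absolute difference: 2.4 percentage points.
- A 14.5% reduction: 0.138 × (1 − 0.145) = 0.118, or 354/3000.

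A one-sided 5% test does not give 14.5% either: its detectable reduction at 80% power with independent students is 15.5%.

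**2. Reproducing the printed rates.** Two-proportion z-test, 3,000 independent students per arm:
- Null SE = √(2 × 0.126 × 0.874/3000) = 0.00857.
- Alternative SE = √((0.138 × 0.862 + 0.114 × 0.886)/3000) = 0.00856.
- Power = Φ((0.024 − 1.96 × 0.00857)/0.00856) = Φ(0.84) = 80.0%.
- Required n for 80% power is 3,001 per arm. Using the counts instead gives 78.8% power.

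The pair 13.8%/11.4% is therefore the detectable difference at a design effect of 1.

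**3. Power for a true 14.5% reduction, still unclustered.** With 11.8%, null SE 0.00863 and alternative SE 0.00862: Φ((0.020 − 1.96 × 0.00863)/0.00862) = Φ(0.36) = 64%. Reaching 80% would need 4,375 per arm.

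**4. Clustering, follow-up comparison only.** Design effect = 1 + 499 × ICC; effective n = 3000/design effect.

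| Assumed ICC | Design effect | Effective n per arm | Power, 13.8% v 11.4% | Detectable reduction at 80% power |
|---|---|---|---|---|
| 0 | 1.0 | 3,000 | 80% | 17% |
| 0.001 | 1.5 | 2,001 | 63% | 21% |
| 0.005 | 3.5 | 858 | 32% | 31% |
| 0.01 | 6.0 | 501 | 21% | 40% |
| 0.02 | 11.0 | 273 | 13% | 52% |

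With a t reference on 10 degrees of freedom, power is about 71% even at ICC = 0.

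**5. The planned difference-in-differences.** Take 500 students per school at each wave, independent students across waves, and a between-wave school correlation r. The variance is the sum over the four arm-by-wave cells of p(1−p) × [ICC(1−r) + (1−ICC)/500]/6. Three cells are at 13.8% and one at 11.4%, so the p(1−p) terms sum to 0.4579.
- ICC = 0: SE = √(0.4579/3000) = 0.01235; power = Φ(0.024/0.01235 − 1.96) = 49%.
- ICC = 0.01: power is 12%, 18%, 28% and 36% for r = 0, 0.5, 0.8 and 0.9. The follow-up-only comparison at the same ICC has 21%.

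Difference-in-differences is thus less precise than the clustered follow-up comparison when schools are unstable between waves, and more precise when they are stable.

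**The case against.** The strongest defence is that the article discloses the dependence on clustering and plans a hierarchical model that accounts for it. That much stands. A reader might infer that the CHKS analysis ignores clustering and that its inference would be invalid; the article does not support that. The fault lies in the planning figure.

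It is also fair that the CHKS section never states 80%, alpha or sidedness. The absence of a clustering allowance is inferred from a numerical match, although a close one (3,001 required against 3,000 available). With a one-sided 5% test, 80% power would survive only up to an ICC of about 0.0005, so the conclusion barely changes.

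A reader might further infer that difference-in-differences doubles the variance on top of the clustering penalty. It does not. Doubling holds only against an unclustered comparison with independent waves; once schools are clustered, differencing removes stable school effects. Independent waves are themselves a pessimistic assumption: many baseline 9th graders would be 11th graders 24 months later. If half the students overlap, with an assumed within-student correlation of 0.3, the unclustered power rises from 49% to about 56%.

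What the defence does not reach is the 14.5%, which no variant reproduces. Nor does the caveat rescue the rates. It reads as if power could move either way with the ICC, whereas ICC = 0 is the favourable limit and any positive value lowers power for the follow-up comparison.

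**Conclusion.** The statement is wrong as written. The contradiction between 14.5% and 17.1–17.4% needs no assumption. That clustering was left out is an inference resting on the .80 and .05 borrowed from the social network section and on a two-sided test. The loss of power is large for small ICCs (63% at 0.001, 21% at 0.01, follow-up comparison), but those ICCs are assumed.

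No replacement detectable effect can be read from the article. By the formula in step 5, the difference-in-differences value at 80% power runs from about 28% (ICC 0.005, r 0.9) to about 60% (ICC 0.02, r 0.5; 58% or 62% depending on the event rates put into the variance). Any single range would only restate the assumptions.

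A reader might also conclude that the whole community-level claim rests on CHKS, or that CHKS must be relabelled as supportive. The article assesses effects at the several levels with the network sample as well as the school data, so neither follows. The point affects what a CHKS result can be said to exclude; it does not affect the estimator or its interval.

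**What to change.** - Delete the 14.5%, or correct it so that the percentage, rates and counts agree.
- Restate the detectable effect for the analysis that is planned: difference-in-differences, 6 versus 6 schools, two anonymous waves of about 500 students per school.
- State the power, alpha and sidedness, the school-level ICC and the assumed between-wave school correlation. The ICC can be estimated from the baseline CHKS data already held.
- Use a reference distribution suited to few clusters, or show a sensitivity range.
- Replace the closing caveat with the result of that calculation, and do not fix a target range beforehand.

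The cost is one recalculation and some rewording, with no new data. The stated detectable effect will be less favourable.

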### Survey Measures for SN and CHKS Data Collection Instruments

#### Overview

All primary and secondary outcome measures for this evaluation are summarized below, with additional details in the Multimedia Appendix 3: measures.

#### Pilot Testing

Instruments for the SN and CHKS data collection and the SN protocol were concurrently pilot tested twice (summer and fall 2021) to ensure feasibility and acceptability. A mix of youth from RPE programs, a 4-H state leadership group, and from high schools in this study’s site communities were recruited for pilot testing (n=24 pilot egos), oversampling LGBTQ+ youth in the second pilot. Recruited pilot testers (ie, pilot egos) took the full SN survey (which contains identical items as the CHKS instrument) online, participated in the SN recruitment process, and then provided feedback on the survey and SN recruitment process during a 60-min talk-back session. In the first pilot test, pilot participants provided feedback on an initial list of name generator questions for SN sampling to help with refinement and consolidation into the final three questions. In the second pilot test, the final name generator questions were tested, as well as the newly developed measures related to LGBTQ+ youth.

Additional key changes made based on pilot testing included adding recorded videos of youth explaining this study to the assent form for alters (because they do not receive an in-person orientation such as egos) and adding the option to return later to provide peers’ contact information. To make inviting peers to participate in a survey easier, we also added a text message template into the survey instructions for participants to use to notify their nominated peers about the survey.

### Primary Outcomes

#### Experiences of SV and DV

SV and DV behaviors were measured by assessing past 12-month and lifetime incidence of virtual or online sexual harassment, in-person sexual harassment and sexual assault, and physical, emotional, and sexual DV (Multimedia Appendix 3: measures). Participants were also asked to indicate if the person who did this to them or who they did this to was a dating or romantic partner. Two items were included for virtual or online sexual harassment; one modified from the Digital Dating Abuse Scale [42] and the other modified from the evaluation of Coaching Boys into Men (CBIM) Victimization Scale [16,40]. Two items were asked for in-person sexual harassment and SV; one modified from the Teen Health and Technology Survey conducted in 2010 to 2011 [41], and the other modified from the CBIM Victimization Scale [16,40]. Two DV items were included, also modified from the CBIM Victimization Scale [16,40]. Measurement of the use of SV by a youth followed the same structure, with inverse prompts and response options. For these items, participants indicate if the behavior was “in-person” or “online.” Items were modified from the CBIM intention to intervene and SV intervention behaviors scales [16,40].

#### LGBTQ+-Targeted Forms of SV and DV

A measure to assess experiences with forms of SV and DV targeting LGBTQ+ youth was developed by the research team. Survey participants who selected an LGBTQ+ sexual and/or gender identity received a module (via skip patterns) that contained items assessing forms of violence targeting LGBTQ+ youth, and those selecting an expansive gender identity (ie, any gender except cisgender boy or girl) received an additional set of items assessing forms of violence targeting gender expansive youth. Items included in these assessments were adapted from two existing scales developed for adults: the Identity Abuse Scale [43] and the Transgender-Specific Intimate Partner Violence Scale [44]. They were reviewed by both practice and research experts on this topic and pilot tested with LGBTQ+ youth.

#### Secondary Outcomes

Secondary outcomes were selected based on our theory of change, including constructs from the guiding theoretical models, TPB and BNI.

Behavioral attitudes related to SV were assessed via a modified version of the Illinois Rape Myth Acceptance Scale, adapted by the evaluation of Green Dot [45,46], consisting of 7 statements related to rape. Previous exploratory and confirmatory factor analyses have demonstrated both reliability (Cronbach α=.94) and construct validity for the Illinois Rape Myth Acceptance Scale in various US settings [45], and preliminary baseline analyses indicated evidence of strong reliability in our sample (Cronbach α=.93). Responses to items were summed and averaged to create a score.

Perceived behavioral control was assessed in the form of confidence in the ability to engage in active bystander behavior. Items for this construct were modified from the intentions to intervene and SV intervention behaviors scales from the evaluation of CBIM [16,40]. Participants were presented with eight SV behaviors and asked, “how confident are you that you could say or do something to stop a friend or another peer who was…” This scale demonstrated evidence of strong reliability in preliminary baseline analyses (Cronbach α=.93).

Behavioral intention to actively intervene to prevent SV was assessed using a modified version of the Intentions to Intervene Scale from the evaluation of CBIM [16,40]. In the modified version for this evaluation, participants were asked how they would react to witnessing four different SV behaviors. Response options include “I would laugh or go along with it,” “I wouldn’t say or do anything,” and “I would say or do something to let them know that I think acting like that is not okay.” Preliminary baseline data indicated evidence of reliability (Cronbach α=.85).

Bystander intervention behaviors were assessed using a modified version of the CBIM SV intervention behavior scale [16,40]. Participants were asked to indicate whether they had witnessed each of eight SV behaviors perpetrated by their peers in the past 12 months and how they responded. This scale demonstrated evidence of reliability in preliminary baseline analyses (Cronbach α=.83).

Social capital, aligned with the construct in the TPB, was assessed in terms of community connectedness and social cohesion because of the way the C2H model aims to build trust, relationships, and collaboration among community members as a mechanism for reducing SV. Community connectedness was measured using four modified items from the Hemingway Measure of Adolescent Connectedness (previously found to be internally reliable at Cronbach α=.73) [47,48]. Participants were asked to identify the community they felt most connected to, and then asked about their connection to this community using two modified items from the Sense of Belonging Scale [49]. Social cohesion was measured using two modified items from the Neighborhood Social Cohesion Scale by Sampson et al [50] and six modified items from the Brief Sense of Community Scale by Peterson et al [51]. These eight items asked about perceived social cohesion in the specific geographic location of the C2H or control community to which the participant was linked. Preliminary baseline data demonstrated reliability (Cronbach α=.88).

Subjective norms related to perceived acceptability of SV and related to perceived likelihood of community members intervening to prevent SV were assessed. These items were developed by the research team based on principles suggested by Cislaghi and Heise [52]. Subjective norms regarding acceptability of SV behaviors were measured via modification of four items of the CBIM Intentions to Intervene Scale [16,40], focused on participants’ self-selected community to which they feel most connected. In preliminary baseline analyses, these items showed evidence of reliability (Cronbach α=.89). Subjective norms regarding perceived likelihood of community members intervening to prevent SV were measured with three additional items that included reference to the geographic community. These items were developed using the Shared Concern Scale by Lippman et al [53] (originally developed for the issue of HIV, with an α of .85). In preliminary baseline analyses, these items showed evidence of reliability (Cronbach α=.92).

### Data Safety and Monitoring Plan

The PI oversaw all data collection procedures, data management systems, and analyses to ensure compliance with all regulatory data safety and monitoring plans, including ethics approval of research protocols, data quality assurance, and safe data storage. At the time of enrollment into this study, individuals were assigned a unique study identifier (a randomly-generated 17-character alphanumeric sequence). Research staff, under the supervision of the PI, maintained a list linking participants’ unique study identifiers with provided contact information (email address and cell phone number) stored as a separate electronic file on an encrypted server that only two members of this study’s team could access and was deleted after follow-up data collection. Data collected at each time point was linked via study identifiers only. SN data collected via Qualtrics was encrypted at all times, including during transit, and was backed up weekly during data collection, and was only accessed by research staff. CHKS data were securely transferred to the research team by WestEd. All computers used to upload, analyze, or store CHKS data did so via university-approved encrypted cloud services and were password-protected. The PI and research staff were responsible for immediately reporting any breaches of protocol, breakdowns in the consent process, violations of confidentiality of the data, complaints by participants, or any serious problems or adverse events to the PI, who was then responsible for filing an incident report with the HRPP within 24 hours. All research staff involved in this study with access to participant data completed Collaborative Institutional Training Initiative training on human participants research in accordance with university policies regarding the protection of human participants.

